### Study variables

The main dependent variable will be the number of hospital falls. A hospital fall will be defined as “the consequence of a non-intentional and sudden movement towards the floor from a more elevated position” in hospital settings.

Other independent variables related with the patient who experiences a hospital fall include: (i) sociodemographic and economic data (age, gender, marital status and level of education); (ii) time (hour and minute, day and shift work) of fall; (iii) patient position (from the bed with or without bedrails, sitting, walking, and so on) and witness of the fall (roommate, family member, healthcare professional or no witness); (iv) use/no use of footwear and kind (open or closed); (v) cause of fall (instability (general instability and balance loss), dizziness (syncope, fainting and cardiovascular accident), drug adverse effects (diuretics, anti-hypertension and other drugs), accident (event with no identifiable cause), ambient-related (dropped objects, obstacles and wet floor), fragility (extreme fragility or weakness) or others); (vi) location of the fall (hospital room, bathroom, corridor, public area or others); (vii) fall-related injuries and severity (no wound/no consequences, minor wounds (grazes and minor contusions), afflicting wounds (contusions requiring stitches, fractures and skull trauma) or others (not afflicting wounds but still in need of minor medical intervention)); (viii) number and kind of coexisting clinical conditions; (ix) prescribed drugs and their time of administration; (x) chronotype measured by the Horne-Östberg Questionnaire (1976); (xi) quality of life in terms of body functionality, physical limitations, body pain, social role or function, mental health, emotional limitations, vitality, energy or fatigue and general perception about own health; and (xii) general health status in terms of somatic symptoms, anxiety, insomnia, social dysfunction and depressive symptoms.

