In the case of healthcare professionals, independent variables will be: (i) sociodemographic and economic data (age, gender, marital status, level of education, work experience and time worked in the unit); (ii) kind of contract and work unit; (iii) sleep pattern (quality and quantity of hours); (iv) chronotype measured by the Horne-Östberg Questionnaire (1976); (v) quality of life in terms of body functionality, physical limitations, body pain, social role or function, mental health, emotional limitations, vitality, energy or fatigue and general perception about own health; (vi) general health status in terms of somatic symptoms, anxiety, insomnia, social dysfunction and depression; and (vii) fatigue/sleepiness, attention and cognitive functionality.

Pre- and post-intervention will be:

***Step 1.*** Before implementing preventive measures: development of audits and seminars in order to improve, secure and control the registration of falls in hospitals and related factors, as well as others study variables (quality of life, functional status, chronotype, fatigue/sleepiness, attention and cognitive functionality). These interventions will be carried out by research nurses who are working in hospitals.

***Step 2.*** Implementation of a preventive measures programme: adjusted to the identification of temporal patterns of falls and relative risk factors of falls. As measures will be agreed with the managers of hospital centres, the interventions will be reflected in the official document of general objectives of the hospitals. Official document to which the personnel involved in the intervention have access. Preventive measures will be focused on organizational, educational and behavioural elements related to older people and healthcare professionals:

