Support and instruction to the patient in preventive health measures (wear suitable footwear and, when necessary, include orthoses; repeated reminders to patients of the need to notify the team for any situation (getting up/lying in bed, going to the bathroom/shower, walking in the hallways, …)).Take extreme measures to prevent falls by healthcare professionals at times related to meals and transfers.Placing a poster encouraging the need to review medication(s) at admission and periodically through patient monitoring.Patient risk management procedures, including post-fall monitoring, alternatives to restrictions and/or restrictive elements, increased number of nursing visits to the patient, promotion of safe mobility and bathing practices based on specific clinical guidelines (Register Nurses’ Association of Ontario, 2011) and use of proper closed footwear.Monitoring and improvement in the distribution of work shifts in healthcare professionals.

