### Data collection: Instruments

***Phases 1 and 2***: Several instruments will be used for data collection. The variables related to the fall and older person will be collected through the fulfilment of a specific record sheet for falls. This record sheet will have to be completed by the patient’s referring nurse (professional who generally records the fall, a fact documented in previous investigations [6]. The registration sheet will be the one attached at the end of this report, similar to that used in a previous project of the research group [20] (ANNEX I). To facilitate this process, an electronic data collection notebook will be hosted on the website of the study hospitals.

On the other hand, the sleep pattern will be measured by means of the Pittsburgh Sleep Quality Index (Spanish version) [29]. The chronotype of each person will be determined using the Horne-Östberg Morningness-Eveningness Questionnaire (Spanish version) [30]. For the quality of life related to health, the 36-Item Short Form Health Survey, version 2 (SF-36v2) (Spanish version) will be used [31], while for the general health status, the 28-Item General Health Questionnaire (GHQ28) (Spanish version) will be used [32]. The variables somnolence, fatigue and speed of response to the event will be measured by means of the Epworth Sleepiness Scale (Spanish version) [33].

With the intention of managing the data appropriately, an electronic data collection notebook will be developed by the Bioinformatics Unit of the Maimonides Institute for Biomedical Research of Córdoba.

***Phase 3***: The focus groups will be constituted with healthcare professionals—doctors, nurses and nursing assistants who provide and have provided their professional services in the field of study in the period previously indicated.

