After obtaining and analysing the falls that occurred during the first 18 months of the study, time-adjusted preventive measures will be carried out. These measures will be focused on organizational, educational and behavioural elements (previously mentioned).

The establishment of the programme of time-adjusted prevention measures will be carried out in May 2019 in the four centres. The post-intervention data collection will cover July 2019 to September 2020. The managers responsible for each centre, together with the research team, will implement the measures, and, as in the first phase, seminars will be held with healthcare professionals to focus on the recording of falls and their circumstances, as well as the variables included in the prevention programme.

During the post-intervention phase, the individual monthly audits will continue to be carried out with each Clinical Management Unit. This follow-up will make it possible to discern the effectiveness of the preventive measures.

***Phase 2***: For the retrospective study, the data will be delivered by the centres participating in the project to the Principal Investigator anonymized.

***Phase 3***: The development of the focus groups will be carried out in the facilities of the participating hospitals, ensuring the confidentiality of the participants. Four focus groups will be held at the Reina Sofia University Hospital in Córdoba and one in each of the three regional centres.

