## Discussion

In a multi-causal adverse event such as a fall, a good initial evaluation of hospitalized elderly people and their registration is necessary. The results of the study, in addition to stimulating the epidemiological investigation of falls, are intended to prevent falls in the hospital setting. Obtaining temporal patterns in hospital falls allows establishing high-risk periods during the day. This fact may correspond to certain activities predictable in time. In this sense, previous studies applied in Italian hospitals have shown that the establishment of time-adjusted preventive measures has led to a decrease in the number of falls [20, 21]. All this will contribute to improvement in the safety of the individual, and as consequence of their health, environment (family environment) and social level (due to the decrease in costs that a decrease in dependency implies) [20].

Furthermore, the study interventions emphasize the importance of recording in-hospital falls and their circumstances, especially time. Therefore, it represents a change in health policy. In previous studies [6], a low incidence of falls has been detected in the hospitals of Andalusia, being less than 1 %, although 65 year olds are the population that suffers the most from these types of events, which is contradictory. Contradiction contrasted with other studies [24], where healthcare professionals showed that there is an underestimation of hospital falls. On the other hand, the previous studies that support the present project [20] found high incidences as a result of an appropriate registry of these events.

Nurses routinely need 24 h per day to care for patients, in many different settings and environments. The impact on physical and psychological well-being of shift work management and lengths of shifts have been largely studied [36, 37]. The findings emerging from these investigations are that anomalies of the circadian rhythm summed with the characteristics of shift workers may have a direct influence on the health of nurses [38]. The outcome to be analysed in the proposed study relate chronotype, sleep quality and health status of the nurse with the quality of clinical practice and ultimately patient safety.

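### The main outcome counts registered falls, but registration is being built up during the baseline and detection may rise with the programme, so the before-after change is not the programme's effect alone

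*Protocol article*

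**What the plan says.** Study variables fixes the outcome: "The main dependent variable will be the number of hospital falls". Data collection: Instruments says that the fall variables are "collected through the fulfilment of a specific record sheet for falls", completed by the patient's referring nurse. What can be analysed is therefore a count of registered falls.

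Step 1, which is the comparison period, is described in Study variables as "development of audits and seminars in order to improve, secure and control the registration of falls in hospitals and related factors". Secondary aim (v) likewise treats effective registration as something to be improved and assessed before and after.

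At the change of step, Data collection: Procedure says that "seminars will be held with healthcare professionals to focus on the recording of falls and their circumstances". The same sentence likens this to the first phase, and the next paragraph continues the monthly audits. The programme measures in Study variables include "increased number of nursing visits to the patient" and post-fall monitoring.

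The programme is set up in all four centres in May 2019. The follow-up audits are said to allow the effectiveness of the preventive measures to be judged. The Background describes falls that go unregistered, and the Discussion notes that earlier work by the group "found high incidences as a result of an appropriate registry of these events".

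**The concern.** The main aim is to measure the effect of the programme on falls. A registered count moves when falling changes and also when the share of falls that reach the sheet changes. By the authors' own account that share is incomplete and matters for the observed incidence.

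Two features of the plan can shift it between the steps:

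- **Baseline build-up.** Step 1 is meant to improve registration, so its early months may be less complete than its later ones.
- **Detection in Step 2.** Recording training is refreshed at the boundary, and more nursing visits and post-fall monitoring can bring to light falls that would otherwise be missed.

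Both raise the recorded Step 2 rate relative to baseline. All centres change at the same time, so no concurrent comparison cancels the shift. At stake is whether a working programme is recognised as one. The Limitations section accepts that the record depends on staff, but not that this dependence may differ between the steps.

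**Working it through.** **Inputs from the document.** Step 1 lasts 18 months (Design). Post-intervention collection runs from July 2019 to September 2020, which is 15 months (Data collection: Procedure). Tests are two-sided at 0.05 (Data analysis). The article gives no fall count, effect size or completeness figure, so there is no figure to reproduce. All completeness values and fall counts below are assumptions.

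**Model.** Let c1 and c2 be the mean shares of true falls registered in Steps 1 and 2. Then recorded rate ratio = true rate ratio × c2/c1.

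**Build-up from 50% to 85%, then flat, with c2 = 0.85**

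- Nine-month build-up: nine evenly spaced monthly values from 0.50 to 0.85 average 0.675. c1 = (9 × 0.675 + 9 × 0.85)/18 = 0.7625, and c2/c1 = 0.85/0.7625 = 1.115. An inert programme shows about +11%. A true 20% reduction is recorded as 0.8 × 1.115 = 0.892, a fall of about 11%.
- Two-month build-up: c1 = (0.50 + 0.85 + 16 × 0.85)/18 = 0.831, and c2/c1 = 1.023. An inert programme shows about +2%. A true 20% reduction is recorded as 0.819, a fall of about 18%.

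**Other build-up assumptions.** Completeness rises linearly from c0 (0.5 or 0.6) to 0.8 over k = 6 to 18 months of Step 1, then stays at 0.8. c1 = [k(c0 + 0.8)/2 + (18 − k) × 0.8]/18.

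- Mildest case, c0 = 0.6 and k = 6: c1 = 0.767, ratio 1.043. A true 0.80 is recorded as 0.835.
- Strongest case, c0 = 0.5 and k = 18: c1 = 0.65, ratio 1.231. A true 0.80 is recorded as 0.985.

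**Added detection in Step 2.** If c2 also rose to 0.95, the nine-month case gives 0.95/0.7625 = 1.246. A true 20% reduction would be recorded as 0.8 × 1.246 = 0.997. This is an extreme illustration. In general, a completeness ratio of 1/0.8 = 1.25 hides a 20% reduction entirely.

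**Effect on the test.** Take n recorded falls in Step 1, Poisson counts, and a Wald test on the log rate ratio. With completeness ratio r and a true ratio of 0.8, m2 = n × (15/18) × 0.8r, SE = √(1/n + 1/m2), and P(significant decrease) = Φ(−1.96 − ln(0.8r)/SE).

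- Example with n = 200 and r = 1.10: m2 = 146.7, SE = 0.109, ln(0.88) = −0.128, probability 22%.
- For n = 100, 200 and 400, the probability is 29%, 51% and 81% at r = 1.0, and 13%, 22% and 38% at r = 1.10.

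**Opposite direction.** If completeness fell, r = 0.90 with no true effect gives a significant false decrease with probability 10%, 16% and 28% for the same n, against a nominal 2.5%. What might cause such a fall is inference only.

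**The case against.** The strongest reply is that the plan holds the recording system constant. One sheet is described, the Step 2 seminars repeat those of Step 1, and the audits continue. This stands. A reader might infer from "seminars will be held with healthcare professionals to focus on the recording of falls and their circumstances" that the method of recording changes between the steps, but in context the sentence shows continuity. The concern is with completeness under the same system.

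Three further readings go beyond the text:

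- **Patients told to report falls.** The programme includes "repeated reminders to patients of the need to notify the team for any situation", but the examples given are movements such as getting up or going to the bathroom. This is a call for help before moving and supports a change in fall reporting only indirectly.
- **Pressure to under-report.** "the interventions will be reflected in the official document of general objectives of the hospitals" puts the measures, not a target for fall numbers, into those objectives. An incentive to record fewer falls is possible but is not stated anywhere.
- **No means of detecting a shift.** Phase 2 collects institutional records from the same hospitals and dates to contrast with the prospective data, aim (v) assesses registration before and after, and triangulation is planned. These are partial checks. No estimate of completeness per step or correction is stated, and the institutional records may come from the same reporters.

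It is also fair that the build-up could be short. The Procedure section describes the seminars before it turns to the start of data collection, whereas Design places them within the 18-month step. Nothing in the article supports nine months in particular, which is why two months is shown as well. Finally, sensitivity analyses are often left to a fuller document. The features that create the imbalance, however, are stated here, and so is the reading of follow-up as showing effectiveness.

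**Conclusion.** The concern holds in a limited form. Registered falls before and after are not comparable without some check on completeness in each step, so the change cannot be attributed to the programme alone. The better supported bias is upward in Step 2 and would mask a benefit. A downward bias cannot be excluded but rests on inference.

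The size is unknown. The +2% to +11% range for an inert programme depends on the assumed 50% and 85%, on the length of the build-up, and on completeness staying at 85% in Step 2. The test probabilities further assume Poisson counts and 100 to 400 recorded baseline falls. The documents do not support a claim that the result is necessarily distorted or that the bias is large. They do support adding inexpensive safeguards around the main aim.

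**What to change.** Before the outcome data are compared, add the following to the analysis, using data already planned:

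1. Pre-specify falls in the record sheet's afflicting-wounds category (stitches, fractures, skull trauma) as a companion outcome. They should be less sensitive to registration habits. Report the rate ratio and 95% interval beside the main result.
2. Repeat the main analysis treating the early Step 1 months, while the first seminars are being delivered, as a run-in.
3. Compare sheet counts with the Phase 2 institutional records by hospital and month, to see whether capture shifted between the steps. State that the two sources may share reporters.
4. If these analyses disagree materially with the main result, describe that result as a change in registered falls.

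Do not adopt a rule that falls were reduced whenever the main and companion estimates point the same way. Under an inert programme, an unbiased injury count points down about half the time. The shares of no-injury and unwitnessed falls can be shown by month, but only descriptively, because the programme itself may change them.

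The cost is some wording and a little analysis, with no new data collection. The companion outcome is less precise: with an assumed 60 and 50 events, the 95% interval is the estimate multiplied and divided by exp(1.96 × √(1/60 + 1/50)) = 1.46. The run-in analysis gives up some baseline months.

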## Abstract

**Background:**

Accidental falls in hospitals are serious events concerning the safety of the patients. Recent studies demonstrated that the time of falls is a key factor to be considered in prevention. It has been shown that the time of day, the day of the week and the month of the year impact on the occurrence of falls. The aim of the study is to determine the effect of the application of a programme of preventive measures based on the temporal patterns of the risk factors on the hospital fall occurrence.

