### Temporal patterns in hospital falls and relative risks of fall

Although important efforts have been made to identify possible risk factors for falls, the time of falls has often been ignored. With regard to the occurrence of accidental falls, it is important to know not only the time of day and the shift work of the healthcare professionals (especially nurses, who are responsible for the data collection) but also the relative risk of intrinsic and external factors (*chronoepidemiology*), as well as circadian rhythms related to the clinical care of patients and healthcare workers [19, 20]. Recent studies of our research group [5, 20, 21] observed that the time of the day, the day of the week and the month of the year have impacts on the fall occurrence. Concretely, a retrospective study [20], carried out in five different non-teaching public Italian hospitals after the development of a programme to prevent falls, identified 24-hour and seasonal patterns for accidental falls in hospitals among a population older than 65 years old and showed crucial information about the relationships between the circumstances of falls (cause, mode and place) and times of falls. On the other hand, the extension of preventive measures according to the obtained temporal patterns (*chronoprevention*) affected the reduction of the number of falls in hospitals, although, due to the retrospective nature of the study and the association with other institutional measures not included in the study, a possible direct effect was not established.

In addition to the research carried out in our group, several studies have been focused on the topic, which is an important indicator of the increasing importance of the research field among the scientific community [22, 23]. Both studies confirmed the finding of a morning peak in hospital falls strictly related to bathing activities. In fact, as consequence of the results published by Magota [23], a letter to the editor was published in order to promote more comprehensive research about accidental falls focused on temporal patterns [24].

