## Methods/design

### Aims

The main aim of this study will measure the effect of the implementation of a falls prevention programme based on temporal patterns and relative risks factors.

Secondary aims will be: (i) to identify temporal patterns in the incidence of hospital falls and intrinsic and external risks factors, pre- and post-intervention; (ii) to establish differences in temporal patterns according to the hospital setting (teaching or non-teaching) and the different types of wards (medical, surgical or mixed), pre- and post-intervention; (iii) to study the role of circadian time in drug administration for older people suffering from hospital falls, pre- and post-intervention; (iv) to identify the level of fatigue/sleepiness, attention and cognitive functionality of healthcare professionals intervening during hospital falls, pre- and post-intervention; and (v) to develop a uniform, simple and intuitive method to record hospital falls in order to improve the effectiveness of the registration of falls and to assess the implementation pre- and post-intervention.

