### Design

A mixed-method research design will be carried out. Three different study designs will be used:

***Phase 1.*** Prospective longitudinal study in two steps:

A first step of 18 months, in which a first intervention of audits and seminars in healthcare professionals will be carried out, focused on an effective and efficient registry of hospital falls in older people. This first phase is crucial to identify temporal patterns of falls in relation to specific intrinsic and extrinsic risk factors among hospitalized older people, as well as the levels of fatigue/sleepiness, attention and cognitive functionality of the healthcare professionals who attend to an in-hospital fall.A second step of application of a multidimensional prevention programme for 15 months focused on organizational, educational and behavioural elements applied to admitted older people and healthcare professionals.

***Phase 2.*** Retrospective study of the fall records found in the institutional databases of the study centres in the period between January 2018 and September 2020. This period covers the first (January 2018–May 2019) and second phases (June 2019–September 2020) of the project, as previously indicated.

***Phase 3.*** Descriptive exploratory study with a qualitative approach, focus groups made up of healthcare professionals: doctors, nurses and nursing assistants who provide and have provided their professional services in the field of study, in the periods in which the longitudinal and retrospective studies have been carried out.

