### Data collection: Procedure

***Phase 1***: The project will be explained to the institutional managers of the centres included in the study, who will appoint a coordinator to ensure proper development and will work in coordination with the research team. In these meetings, the process of recording falls will be disclosed, as well as the other variables.

Prior to data collection, meetings will be held with those responsible for the Clinical Management Units and special mention will be made of the areas that are expected to have a greater number of events (internal medicine, neurology, trauma, rehabilitation, …). Additionally, the dynamics of data collection will be explained.

On the other hand, being focused more on healthcare professionals (especially nurses) from the different study centres, several seminars will be held (first intervention), explaining how data collection should be done, as well as the definition of variables included in the record sheet. Such seminars will be proportional to the number of workers in the different centres included, being distributed over different days so that the number of workers receiving information is as large as possible. In addition, specific audits will also be carried out in each Clinical Management Unit.

During the first 18 months of study development, each time a fall occurs, in addition to recording the circumstances of the fall, it is necessary to obtain the informed consent of the patient to know their quality of life, general functional status, sleep pattern and chronotype. In healthcare professionals, informed consent must also be obtained to know the previous variables, as well as the values of fatigue/sleepiness, attention and cognitive functionality. In this sense, as it has been commented on in the inclusion/exclusion criteria, these variables will only be known in the healthcare professionals responsible for the older person, who have visualized and/or attended the fall event, even though the fall may be the result of a collective lack of attention from all the staff and not from a single person.

Once the prospective data collection period has started (January 2018), monthly individualized audits will be carried out in the different Clinical Management Units, aimed at managing correct data collection. Furthermore, these audits will allow obtaining a perspective of the fall event in relation to the number and related circumstances.

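### The before-after windows hold different calendar months and no season or trend term is stated, so season and trend cannot be separated from the programme effect

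*Protocol article*

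**What the plan says.** The main aim (Aims) is to "measure the effect of the implementation of a falls prevention programme based on temporal patterns" and related risk factors. The outcome is a count: "The main dependent variable will be the number of hospital falls" (Study variables).

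The timetable is in Design and in Data collection: Procedure. The pre-programme period is "A first step of 18 months, in which a first intervention of audits and seminars in healthcare professionals will be carried out", and prospective collection starts in January 2018. The programme is set up in May 2019 in all four centres. Then "The post-intervention data collection will cover July 2019 to September 2020", which is 15 months. The Phase 2 paragraph of Design dates the two project phases differently: January 2018 to May 2019, and June 2019 to September 2020.

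No centre stays without the programme and the start is not staggered. The Phase 2 institutional records come from the same four hospitals and the same period, so they supply neither an outside control nor a longer baseline.

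On season, the Abstract says that the time of day, "the day of the week and the month of the year impact on the occurrence of falls". The Background adds that an earlier retrospective study by the group "identified 24-hour and seasonal patterns for accidental falls in hospitals among a population older than 65 years old".

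Data analysis names t tests, chi-square or Fisher tests, one-way ANOVA, Pearson correlation and a multivariate logistic regression whose covariates are not given. Cosinor analysis is there to explore temporal patterns. Neither season nor time trend is named as an adjustment of the pre/post comparison. Of the post-programme follow-up the article says: "This follow-up will make it possible to discern the effectiveness of the preventive measures".

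**The concern.** In an uncontrolled before-after study, anything that differs between the periods is confounded with the intervention. Two such differences are visible in this plan.

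The first is season. The article holds that falls vary by month, but the two windows weight the months differently.

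The second is trend. All centres switch together, so there is no concurrent series to show what would have happened anyway. A trend in recorded falls is plausible on the article's own account, because the first step consists of audits and seminars meant to improve recording, and recording may change as they take hold.

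A simple two-group comparison has nothing with which to take either out. The main-aim estimate is at stake: a difference in rates could be reported as the programme's effect when part or all of it is calendar, or a real benefit could be masked.

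**Working it through.** **Stated lengths.** January 2018 to June 2019 is 18 months. July 2019 to September 2020 is 15 months. The total is 33, so the article's 18 and 15 reproduce.

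**Month mix.**

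| Months | 18-month pre | 15-month post | 17-month pre | 16-month post |
|---|---|---|---|---|
| Jan-Jun | 12/18 = 66.7% | 6/15 = 40.0% | 11/17 = 64.7% | 7/16 = 43.8% |
| Jul-Sep | 3/18 = 16.7% | 6/15 = 40.0% | 3/17 = 17.6% | 6/16 = 37.5% |
| Oct-Dec | 3/18 = 16.7% | 3/15 = 20.0% | 3/17 = 17.6% | 3/16 = 18.8% |

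The mix is unequal under either set of dates.

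**Effect of season alone.** Assume no programme effect, no trend, equal patient-days each month and a monthly rate proportional to

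s(m) = 1 + A cos(2π(m − p)/12),

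where m is mid-month position (January = 0.5), p the peak and A the semi-amplitude. Neither A nor p is in the article, so A = 10%, 20% and 30% are assumptions and p is varied over the whole year. The spurious rate ratio is

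RR = [Σ n_post(m) s(m) / 15] / [Σ n_pre(m) s(m) / 18],

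with n the number of times each calendar month occurs in the window.

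Worked case, A = 20% and a mid-March peak (p = 2.5): the pre mean of s is 1.0415 and the post mean is 0.9685, so RR = 0.9685/1.0415 = 0.93. With a mid-September peak (p = 8.5) the means are 0.9585 and 1.0315, so RR = 1.08. With a mid-June peak (p = 5.5) they are 1.0111 and 1.0182, so RR = 1.01, which is almost no distortion.

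| A (assumed) | Lowest RR (peak about March) | Highest RR (peak about September) |
|---|---|---|
| 10% | 0.96 | 1.04 |
| 20% | 0.93 | 1.08 |
| 30% | 0.90 | 1.12 |

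Under the 17/16-month dates the ranges are 0.96-1.04, 0.92-1.08 and 0.89-1.13.

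**Link to the article's amplitude scale.** Data analysis defines amplitude as peak minus valley, so the percentage amplitude there is 2A. Its upper limit for low variation (25) is A = 12.5%, giving 0.96-1.05. Its upper limit for moderate variation (50) is A = 25%, giving 0.91-1.10.

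**Effect of trend alone.** The window midpoints are month 9 and month 18 + 7.5 = 25.5, which is 16.5 months apart. An assumed trend of −5% a year gives 0.95^(16.5/12) = 0.93. An assumed +5% gives 1.05^(16.5/12) = 1.07.

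**Check that matching removes the seasonal part.** Comparing July 2018-June 2019 with July 2019-June 2020 gives a ratio of 0.999-1.001 for any peak, even at A = 50%. Matching does nothing about trend.

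**The case against.** The strongest reply is that this is a condensed article. Covariates, harmonics and offsets usually belong in an analysis plan that is not shown, and the unspecified multivariate logistic regression might carry some adjustment. That stands as a caution: it is not shown that the sponsor will ignore season. But the window dates, the simultaneous start and the lack of a control are design choices fixed here, and the analyses that are named do not separate season or trend from the programme. The Limitations section concedes in general that a clinical trial could be less biased. It names neither season nor trend.

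Three stronger readings are tempting and are not supported:

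- **That season and trend will flatter the programme.** With no amplitude or peak month given for these hospitals, the distortion can go either way, and for some peak months it nearly vanishes. The ranges above are worst cases over the peak.
- **That unequal month coverage must corrupt the Cosinor results.** An artificial annual rhythm would arise only if counts were pooled by calendar month without allowing for how many months contribute. The article does not say it will do that. It describes fitting a time series and expresses peak and valley relative to local midnight.
- **That hospital activity in 2020 was unusual.** Part of the post window falls in that year, but the article says nothing about it, so the point rests on nothing in the document.

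**Conclusion.** The concern holds in a limited form. The main-aim comparison is an uncontrolled before-after contrast with a simultaneous start and windows of unequal month mix. It sits in a study premised on seasonal falls, and no season or trend adjustment is stated. The programme effect is therefore not identifiable separately from season and trend with the methods listed, and the claim that follow-up will reveal effectiveness is too firm.

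The size depends on assumptions. For a seasonal semi-amplitude of 10-30%, season alone could move the rate ratio by at most about 4% to 12% in either direction; the exact figures assume a sinusoidal season and equal monthly patient-days. Trend adds a separate and unknown amount. The unequal month mix itself needs no assumption and survives under both sets of dates.

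**What to change.** - Make the primary analysis a segmented count regression of monthly falls per hospital. Include a log patient-days offset, hospital effects, annual harmonic (or calendar-month) terms, a pre-programme trend, and a change in level and slope at programme start, with allowance for autocorrelation. Harmonics are the more economical choice: one sine-cosine pair costs two parameters, against eleven for calendar months, and only six calendar months occur twice before the programme.
- Add a season-matched sensitivity comparison, for example July 2018-April 2019 against July 2019-April 2020. It also avoids May-June 2019, which the article leaves unclear between before and after.
- Reconcile the 18/15-month and 17/16-month dates, and define the programme start used in the model.
- Reword the statement on effectiveness. Say that the comparison is adjusted for season and trend but has no concurrent control, so other changes at the same time cannot be excluded.
- If falls are summarised by calendar month for an annual Cosinor, use rates per patient-day (or per contributing month) rather than pooled counts.

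The cost is modest modelling work, patient-days from hospital records, and a wider confidence interval than a simple before-after test would give. The falls are already recorded with their dates, so no new fall data are needed.
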